### Comparison

Patients in the control group will not receive the HRQoL intervention, but will receive etanercept treatment only. The consultation will be conducted according to routine clinical practice, or usual care. Dermatologists in the control group will be asked to stay naive to HRQoL assessment and communication during the course of this study; that is, they are not to implement electronic HRQoL assessment with and communication about the Skindex-29 during their consultations with study participants.

#### Outcome measures

The primary outcome parameters in this study are 1) the impact of the HRQoL intervention on patients’ HRQoL and 2) the effect of the HRQoL intervention on doctor-patient communication. Since the Skindex-29 is used as the intervention questionnaire, the impact on HRQoL will be measured with another dermatology-specific HRQoL questionnaire, namely the Dermatology Life Quality Index (DLQI). The DLQI consists of ten items and each item is scored on a four-point scale ranging from ‘not at all/not relevant’ to ‘very much’. Scores of individual items (0 to 3) are added to yield a total score (0 to 30). Higher scores mean greater impairment of a patient’s HRQoL [23,24]. A study-specific, two-dimensional communication questionnaire will be used to measure the effect on doctor-patient communication. This communication questionnaire consists of two parts, measuring: 1) the satisfaction with doctor-patient communication and 2) the quantity of HRQoL communication during consultations. With approval from the authors, the first part of the communication questionnaire is a slightly adapted version of the Patient Satisfaction Questionnaire and includes items on satisfaction with information, (emotional) support, communication, and fulfillment of needs [25]. Answers are given on a visual analogue scale (VAS) ranging from 0 to 10, for example, ‘not at all satisfied’ to ‘very much satisfied’, or ‘not at all important’ to ‘very much important’. The cut-off point for satisfaction will be 6.0 (60%). The second part of the communication questionnaire includes items on symptoms, mood or emotions, social functioning, and overall quality-of-life. Patients will be asked if these aspects were discussed during the patient consultation or not, by ticking ‘yes’, ‘no’, or ‘I don’t know’. The communication questionnaire was successfully pilot tested in seven in-patients with psoriasis at the Academic Medical Center, Amsterdam.

The secondary efficacy endpoints include health status and disease severity. Health status will be measured with the Medical Outcomes Study 36-item Short-Form General Health Survey (SF-36), a well-established, eight-dimensional, generic HRQoL instrument [26,27]. The items represent issues relevant to health status, and relate to the past four weeks. The SF-36 will be completed at week 0 (V1), week 24 (V4), and week 48 (V6) by patients in both the intervention and control group. Disease severity will be measured with the PASI, the most widely used instrument for the measurement of the severity of psoriasis [28], and with an investigator global assessment (IGA) and a patient global assessment (PGA). The IGA is asking dermatologists: ‘In your opinion, how severe is your patient’s current skin condition?’, and the PGA is asking patients: ‘How severe is your current skin condition?’. Answers can be given on a five-point scale, ranging from ‘not severe’ to ‘very severe’. All patients will be asked to complete this set of questionnaires at the end of each patient consultation.

In addition, two evaluation questionnaires will be introduced to measure 1) aspects on satisfaction and 2) aspects on the feasibility of HRQoL assessment and communication in dermatology practice. First, at week 24 (V4) and week 48 (V6), an overall evaluation questionnaire will be handed to dermatologists in the intervention group, and to patients in both the intervention and the control group. This questionnaire comprises a study-specific questionnaire about 1) satisfaction with the treatment process, including doctor-patient communication, and 2) satisfaction with treatment outcomes. For example, ‘How satisfied are you about the conversations you have had with your doctor/patient?’. Answers are given on a VAS, ranging from ‘not at all satisfied’ to ‘very much satisfied’. Second, after each patient consultation, dermatologists in the intervention group will be asked to answer questions on aspects of feasibility, such as completion time, duration of the consultations, and (the number of) aspects of HRQoL discussed during the consultations. Dermatologist in the control group will only be asked about the duration of the consultations.

#### Data collection

A Case Report Form (CRF) will be provided for each patient. All protocol-required information that needs to be collected during this study will be entered by the dermatologist, or a designated representative. Baseline characteristics will be obtained at visit 1 (week 0).

#### Safety

All patients will be monitored for safety during their participation in the study, including adverse events (AEs) and premature discontinuation from the study. AEs are defined as any undesirable experience occurring to a patient during the study, whether or not considered related to etanercept. Serious adverse events (SAEs) will be recorded by the responsible dermatologist and reported within 24 hours of notification to the trade holder of etanercept. According to the Dutch Personal Data Protection Act, all data will be handled confidentially and anonymously, and will be stored for 15 years after study close out (that is, last patient last visit).

### Analysis

#### Power calculation

The sample size calculation is based on the two primary outcome parameters and its corresponding outcomes measures, namely the DLQI and the communication questionnaire.

Based on previous research, we will expect a HRQoL improvement, as measured with the DLQI, of 1.0 standard deviation (SD) in the intervention group and of 0.7 in the control group. We expect a communication effect size of 0.8 (that is, an improvement of 0.8 SD) in the intervention group, and of 0.4 in the control group. With 100 patients in each group, the power to detect a longitudinal effect would be larger than 99%, assuming a significance level of 5% and an autocorrelation (that is, the correlation between scores at baseline and end of induction phase) of 0.5.

The power to detect differences in longitudinal DLQI effects between the intervention and control group will be 56%. In case of one-tailed testing, the power to detect differences in longitudinal DLQI effects between the intervention and control group will be 68%. A mean DLQI score of 12.0 (SD 7.0), and a clinically meaningful improvement of 5 points is expected. In the intervention group, an additional improvement of 2 points (effect size: 0.3) is expected.

The power to detect differences in longitudinal communication effects between the intervention and control group is 80%. The power calculation is conservatively based on an estimate of 200 patients; that is, it is based on 100 patients per group and an expected withdrawal rate of approximately 20%.

#### Statistical analysis

Statistical analyses will comprise two components: 1) the induction phase analysis (week 0 to week 24) and 2) the maintenance phase analysis (week 24 to 48).

The induction phase analysis will concern all patients who receive any treatment with etanercept, who respond to the study questionnaires on HRQoL, communication, health status, and disease severity, and of whom PASI is assessed at baseline. The last visit of patients who may discontinue from treatment for any reason, including patients who will not meet the criteria to continue treatment with etanercept after week 12 (PASI <50), will be considered as End of Induction Phase (week 24).

The maintenance phase analysis will concern all patients who receive any treatment with etanercept after week 24, who respond to the questionnaires, and of whom PASI is assessed at week 24. The last visit of patients, who may discontinue from treatment for any reason, will be considered as End of Maintenance Phase as well as End of Treatment (week 48).

All analyses will be performed on an intention-to-treat basis. In any case where patients prematurely discontinue from treatment, they will be asked to complete an Early Termination visit. The content of this visit is similar to V6, and data will be handled based on the ‘last value carried forward’ principle.

Patient characteristics will be described by randomized groups. Categorical data will be summarized as frequencies and percentages. Continuous data will be summarized by means and standard deviations. Linear mixed model analysis will be used to investigate the course of the outcomes (that is, DLQI scores for HRQoL; communication scores for doctor-patient communication; SF-36 scores for health status; and PASI, IGA, and PGA for disease severity), and to test the effects of possible explanatory variables on the outcome variables. Longitudinal models will have a random intercept to account for individual differences at baseline, fixed regression coefficients for each of the measurement occasions following baseline, for the intervention effect, for study sites (to account for differences between sites), and for possible other explanatory variables (such as age and sex). We will investigate which longitudinal structure is most appropriate, whether one or more of the fixed regression coefficients should be considered random, and whether there are interaction effects.

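### Relabelling a discontinuer's last visit as week 24 or week 48 and carrying the value forward can bias the visit-specific group contrast, and the planned mixed model does not need it

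*Protocol article*

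**What the plan says.** All of the following is in the protocol article, Statistical analysis.

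- **Induction phase.** The last visit of patients who stop for any reason, including those who do not "meet the criteria to continue treatment with etanercept after week 12 (PASI <50), will be considered as End of Induction Phase (week 24", takes the place of the week-24 visit.
- **Maintenance phase.** The last visit of a patient who stops "will be considered as End of Maintenance Phase as well as End of Treatment (week 48".
- **Data at stopping.** Patients who stop early are told that "they will be asked to complete an Early Termination visit". The rule continues: "The content of this visit is similar to V6, and data will be handled based on the" principle of "last value carried forward".
- **Principle.** "All analyses will be performed on an intention-to-treat basis".
- **Model.** "Linear mixed model analysis will be used to investigate the course of the outcomes". It has a random intercept, a fixed coefficient for each measurement occasion after baseline and one for the intervention effect. Interactions are to be investigated.

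The Design section sets visits at weeks 0, 6, 12, 24, 36 and 48. The Power calculation section expects about 20% withdrawal and does not split it by arm or by time.

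**The concern.** A score recorded at week 6, at week 12 or at an early-termination visit between scheduled visits is entered as the week-24 score; after week 24 the same is done for week 48. The model estimates a separate level for each occasion, so the week-24 level would be built partly from earlier measurements. Two assumptions come with this: a patient does not change after stopping, and a copied value carries as much information as a measured one.

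Several features of the design make the first assumption doubtful.

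- Stopping is partly driven by response, through the week-12 PASI criterion (Participants).
- Dermatologists and patients are unblinded (Design), and actual dosing follows local practice (Participants), so withdrawal could differ between arms.
- The intervention accumulates: material is added at each of the first five consultations (Intervention), so a week-12 score need not show the week-24 effect.

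For the second primary outcome, the communication questionnaire asks whether topics were discussed during the consultation (Outcome measures). Carrying it forward scores a later consultation that may not have taken place.

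At stake is the size, and possibly the direction, of a between-group DLQI contrast that is expected to be only 2 points.

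**Working it through.** **Inputs from Power calculation.** 100 patients per group; DLQI improvement 1.0 SD against 0.7 SD, a difference of 0.3 SD; DLQI SD 7.0; additional improvement 2 points; correlation between baseline and end of induction 0.5; two-sided 5%; withdrawal about 20%.

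**The plan's own figure.** SD of change = √(2(1 − 0.5)) = 1.0 SD. The standard error of the difference is √(2/100) = 0.1414. Power = Φ(0.3/0.1414 − 1.96) = 56.4% (stated 56%). One-tailed it is 68.3% (stated 68%). With 0.4 SD for communication it is 80.7% (stated 80%). The figures reproduce with 100 analysed per group on a baseline to end-of-induction change. This is why week 24 is used below, although the article names no primary time point.

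**Equal withdrawal, effect still building.** Let d be the share who stop before week 24, the same in both arms, and f the share of the week-24 difference already present at the last visit. With carry-forward the expected contrast is 0.30(1 − d) + 0.30·f·d. With d = 0.20, all assumed to fall before week 24:

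| f | Contrast (SD) | On the 2-point scale |
|---|---|---|
| 0 | 0.24 | 0.8 × 2 = 1.6 |
| 0.5 | 0.27 | 0.8 × 2 + 0.2 × 1 = 1.8 |
| 1 | 0.30 | 2.0 |

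If part of the 20% withdraws after week 24, the week-24 dilution is smaller.

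**Unequal withdrawal.** Bias = (difference in withdrawal) × (gap between the carried and the true week-24 value). With an assumed 10-point difference and an assumed gap of 3 to 5 DLQI points: 0.10 × 3 = 0.3 and 0.10 × 5 = 0.5 points, or 15% to 25% of the 2-point effect. The sign depends on which arm loses more patients and on the direction of the gap.

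**Simulation of a more extreme split.** Assumptions: correlation 0.5; control improvement 0, 0.4, 0.5 and 0.7 SD at weeks 0, 6, 12 and 24; stopping after week 12 more likely with a poor observed week-12 change.

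| True week-24 effect (SD) | Withdrawal, intervention / control | Carry-forward | Likelihood, observed visits |
|---|---|---|---|
| 0 | 20% / 20% | 0.00 | 0.00 |
| 0 | 10% / 30% | +0.10 | 0.00 |
| 0 | 30% / 10% | −0.10 | 0.00 |
| 0.30, constant | 20% / 20% | 0.30 | 0.30 |
| 0.30, constant | 10% / 30% | 0.40 | 0.30 |
| 0.30, constant | 30% / 10% | 0.20 | 0.30 |
| 0.30, building from 0.15 at week 12 | 20% / 20% | 0.27 | 0.30 |
| 0.30, building from 0.15 at week 12 | 10% / 30% | 0.39 | 0.30 |
| 0.30, building from 0.15 at week 12 | 30% / 10% | 0.15 | 0.30 |

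A shift of 0.10 SD is 0.10 × 7 = 0.7 DLQI points. The likelihood column returns the truth because the simulated stopping depends only on scores that were observed; it is no evidence for missing-not-at-random settings.

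**Single effect averaged over visits.** With about 21% response-related withdrawal after week 12, equal between arms, and the effect half built at week 12, a common intervention coefficient was 0.178 SD with complete data, 0.171 with carry-forward and 0.167 from observed visits only. Here the rule does little harm. In the same simulation the week-24 contrast under carry-forward was 0.28 against 0.30 SD.

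**Precision.** There too, the model-based standard error of the week-24 contrast was 0.122 against an empirical SD of 0.136 with carry-forward, and 0.135 against 0.141 from observed visits. Filled values make the error look too small, but modestly.

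**The case against.** A reader might infer that the rule biases the primary result as such. The documents do not support that. Bias is nil when withdrawal is equal between arms and the effect is constant or absent, and its direction cannot be fixed in advance. Nor does the article say that the primary contrast is at week 24; that comes only from the correlation used in the power calculation. The model text lists one intervention coefficient, with interactions only to be explored, and an effect averaged over visits is affected far less.

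A reader might also infer that those who stop are mostly non-responders. The rule covers stopping for any reason, and no figure gives the mix. The carried value need not be an old one either, because an early-termination visit is requested and may supply a score taken at stopping. The withdrawal splits, the 3 to 5 point gap and the half-built effect are all assumptions. The plan's 5-point meaningful improvement is not evidence of drift after stopping.

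Finally, a mixed model on observed visits alone describes what would have happened had patients continued, which is not automatically nearer to intention-to-treat.

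All of this stands as a limit on the size and certainty of the harm. It does not defend the rule. The article itself fixes the relabelling and the carry-forward, so this is not a detail left to an analysis plan, and the stated model can do without both.

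**Conclusion.** The point holds in a conditional form. The rule places earlier scores in later visit cells of a model that has its own coefficient for each visit, and it treats them as measured. It can dilute or shift the visit-specific contrast if the effect is still building or if withdrawal differs between arms. Under the assumptions shown, the dilution is 0 to 0.4 of 2 DLQI points with 20% equal withdrawal before week 24, and the shift is 0.3 to 0.5 points, in either direction, with a 10-point withdrawal gap. These are illustrations, not estimates for this trial. The understated standard error is a secondary matter. The change is worth making because it costs little and removes an assumption that the analysis does not need.

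**What to change.** 1. For the primary analyses of both the DLQI and the communication questionnaire, delete the relabelling and carry-forward rules. Fit the mixed model to observed values at their actual time, and assign early-termination values by a prespecified visit window.
2. Account for PASI and other observed predictors of stopping, so that missing-at-random is plausible. A joint model or multiple imputation by arm does this better than a post-baseline PASI covariate, which could absorb part of the intervention effect.
3. Keep carry-forward as a sensitivity analysis and add a delta-adjusted one.
4. Where feasible, ask patients who stop etanercept to complete the DLQI at the scheduled times. The randomised factor is the HRQoL intervention, so these scores serve the stated intention-to-treat aim. This does not extend to the communication questionnaire when there is no consultation.

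Items 1 to 3 cost analysis wording, some analysis work and slightly wider confidence intervals. Item 4 is a small procedural addition; the article reports recruitment as ongoing, so it could still apply to part of the sample. No treatment-stopping rule is changed.

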### Participants

Psoriasis patients who will receive etanercept treatment by prescription from their dermatologists will be asked to participate in the study [11-14]. Thus, all included patients of both the intervention and control group will receive etanercept, as a constant factor, in accordance with routine clinical practice and, ideally, following the Dutch treatment guidelines for psoriasis: a PASI ≥8; ineffective or contra-indications to PUVA treatment twice weekly for 10 weeks; ineffective or contra-indications to treatment with cyclosporine 3-5 mg/kg/day for 16 weeks; and/or ineffective or contra-indications to treatment with methotrexate 22.5 mg/day for 16 weeks [15]. The per-protocol dose regimen of etanercept in week 0 to 12 (V1 to V3) is in accordance with the current Dutch summary of product characteristics (SmPC), namely: 2 x 50 mg/week. Depending on the PASI as measured at week 12 (V3), patients either discontinue treatment in case of PASI <50, or continue treatment during week 12 to 24 (V3 to V4). This treatment phase is called the induction phase. If PASI <75, patients will continue treatment with etanercept with 2 x 50 mg/week; if PASI ≥75, patients will continue with 2 x 25 or 1 x 50 mg/week. However, current clinical practice showed that a growing number of Dutch dermatologists continue treatment directly after the maximum treatment period of 24 weeks. Supporting evidence was found for an entire dosage regimen (week 0 to 48) in the British Association of Dermatologists Guidelines, in the German guidelines for systemic therapy, and in a study on the long-term safety and efficacy of 2 x 50 mg/week [16-19]. Per study protocol, patients will continue treatment during week 24 to 48 (V4 to V6), with 2 x 25 or 1 x 50 mg/week, which is called the maintenance phase (see Figure 2). The dosing schedule as suggested per protocol will be used as a guide for dermatologists. However, the actual dosing schedule to be given to patients will depend on routine clinical practice and the dermatologists’ prescriptions. Previous treatment with any biologic is allowed, taking the applicable wash-out period into account prior to treatment with etanercept. Concomitant topical treatment will be permitted.

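### The week 24 to 48 comparison is restricted by three conditions arising after randomisation, so it is not the intention-to-treat analysis that the plan says it is

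*Protocol article*

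**What the plan says.** The Statistical analysis section of the protocol article splits the analysis into an induction phase (weeks 0 to 24) and a maintenance phase (weeks 24 to 48). For the second it says: "The maintenance phase analysis will concern all patients who receive any treatment with etanercept after week 24, who respond to the questionnaires", and adds a further condition, "and of whom PASI is assessed at week 24". Patients who stop earlier have their last visit counted as the end of induction. This includes those stopped under the week-12 rule in the Participants section, by which "patients either discontinue treatment in case of PASI <50, or continue treatment during week 12 to 24".

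The same Statistical analysis section then states: "All analyses will be performed on an intention-to-treat basis". It adds an Early Termination visit and carrying the last value forward for patients who stop. The mixed model, with a term for the intervention, is described for all outcomes, and neither phase is exempted.

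The Design section randomises study sites to the HRQoL intervention. Etanercept is background treatment in both arms, and nobody is blinded. On prescribing, the Participants section says that "the actual dosing schedule to be given to patients will depend on routine clinical practice".

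**The concern.** An intention-to-treat comparison counts patients by allocation, whatever happens to them later. The maintenance set instead counts those who are still receiving a background drug, still answering questionnaires and still being scored at week 24. The randomised intervention could influence any of these. It includes material on coping and disease management and a structured discussion of scores, delivered by unblinded dermatologists whose prescribing follows routine practice. Continuation is also tied to response through the week-12 PASI rule.

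Suppose one arm keeps more of its less-well patients than the other. The two retained groups then differ for reasons other than the intervention's effect on quality of life, and the difference would be reported as a randomised effect because of the label.

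**Working it through.** **1. The text.** Each entry condition is set against the time it is decided.

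| Condition | Decided |
|---|---|
| Etanercept after week 24 | After randomisation |
| Response to questionnaires | After randomisation |
| PASI assessed at week 24 | After randomisation |

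The Early Termination visit and carry-forward supply values for patients who stop. They do not bring back a patient who stopped before week 24, because that patient still fails the first condition. Nothing in the article gives intention-to-treat another meaning or calls the maintenance analysis conditional or descriptive. The conflict therefore stands on the wording alone.

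**2. The plan's own figures.** The Power calculation section gives 100 per group, a 5% level, an autocorrelation of 0.5, and differences of 0.3 SD (DLQI: 1.0 less 0.7) and 0.4 SD (communication: 0.8 less 0.4). The SD of change is √(2 × (1 − 0.5)) = 1 SD, and power is Φ(δ√(100/2) − z).

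- DLQI, two-sided: Φ(0.3 × 7.071 − 1.960) = 56.4% (stated 56%).
- DLQI, one-sided: Φ(0.3 × 7.071 − 1.645) = 68.3% (stated 68%).
- Communication: Φ(0.4 × 7.071 − 1.960) = 80.7% (stated 80%).

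These reproduce. The autocorrelation is defined from baseline to the end of induction, so they do not describe the maintenance comparison.

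**3. Possible size of the bias, with no true effect.** From the article: DLQI SD 7.0 and planned extra benefit 2 points. Assumed: staying in the set follows a normal propensity whose correlation with DLQI benefit at week 24 is r = 0.3 to 0.7; retention is 85% in one arm and 70% in the other; the week 24 to week 48 correlation is 0.5; and retention depends on week-48 DLQI only through week 24.

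The mean shift among retained patients is SD × r × λ(p), where λ(p) = φ(z_p)/p.

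- λ(0.85) = 0.2743, λ(0.70) = 0.4967, difference 0.2224.
- Week-24 level difference: 7 × r × 0.2224 = 0.47, 0.78 and 1.09 points for r = 0.3, 0.5 and 0.7.
- Week-48 level difference: 0.5 × those values = 0.23, 0.39 and 0.54 points. The better-retained arm looks worse.
- Week 24 to 48 change: the same sizes with the opposite sign. The better-retained arm looks better.
- Relative to 2 points: 0.23/2 = 12% and 0.54/2 = 27%.

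With equal retention and the same mechanism in both arms, the λ terms cancel and the bias is zero.

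**4. If a true 2-point benefit drives retention.** Assume 75% retention in controls. Retention in the intervention arm is Φ(0.6745 + r × 2/7).

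- r = 0.5: retention 79.3%; λ falls from 0.4237 to 0.3602. The week-24 difference among retained patients is 2 − 7 × 0.5 × 0.0635 = 1.78 points.
- r = 0.7: retention 80.9%; λ falls to 0.3364. The difference is 2 − 7 × 0.7 × 0.0873 = 1.57 points.

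In this scenario the retention gap is 4 to 6 percentage points, and the week-24 benefit is understated by 0.22 to 0.43 points.

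**The case against.** The strongest defence concerns weight. Etanercept is common to both arms under the same week-12 rule, and the article gives a single withdrawal rate of about 20%, not split by arm. The 15-point gap in step 3 has no source in the documents. Step 4 shows that a full planned benefit acting through retention produces a much smaller gap and understates the week-24 benefit. The power calculation concerns the induction phase. An on-treatment maintenance set is also a reasonable way to describe the course of HRQoL under treatment, which the Background lists as an aim.

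All of this stands, and it lowers the severity. It does not remove the conflict: the article names no primary time point, ranks neither phase, and applies the intention-to-treat label to both.

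Two stronger readings are tempting but unsupported. The first is that whole sites could vanish from the maintenance set, because the Participants section says that "a growing number of Dutch dermatologists continue treatment directly after the maximum treatment period of 24 weeks". That sentence introduces the reason for planning continuation, and the same section then says that patients continue from week 24 to 48 under the protocol. The schedule is only a guide, so some patients may stop, but loss of whole sites is conjecture. The second is that the bias could reach 54% of the planned effect (1.09/2). That is the week-24 level difference. For the weeks that this component assesses, the same assumptions give at most 27%.

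**Conclusion.** The point holds as a should-fix. The maintenance set is conditioned on three post-randomisation events and is wrongly described as intention-to-treat, so its comparison between arms lacks the protection of randomisation. That conclusion needs no assumption.

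The size does. The illustrative 0.23 to 0.54 DLQI points depend on the assumed retention gap, selection correlation and week 24 to 48 correlation. Neither the presence nor the direction of bias in this trial can be known from the documents. A reader should not infer that the maintenance result will be a false positive.

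**What to change.** For the between-arm effect at weeks 36 and 48, analyse every enrolled patient in the arm of their site. Use one longitudinal mixed model that holds all observed visits from week 0, with the Early Termination visit entered at its actual time. State the missing-at-random assumption, and let this model replace carry-forward in this analysis. Remove the three entry conditions from it.

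Keep the present continuer set as a supportive analysis, described as conditional on continuing and responding, and without the intention-to-treat label.

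The cost is revised analysis wording and one supportive table. No added patients or visits are needed, and no treatment rule changes. The drawback is that the article describes no visits after Early Termination, so for patients who stop early the week 36 and 48 estimates rest on the missing-at-random assumption. Recruitment was still under way at publication, so the wording could be settled before the analysis.

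### The mixed model as listed has one intervention coefficient and no fixed intervention-by-visit term, so it does not name the difference in change on which the trial is powered, and it leaves the baseline DLQI unused

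*Protocol article*

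**What the plan says.** The Power calculation section of the protocol article expects a DLQI improvement "of 1.0 standard deviation (SD) in the intervention group and of 0.7 in the control group". It assumes 100 patients per group, a 5% significance level and a correlation of 0.5, defined as "the correlation between scores at baseline and end of induction phase". It then states: "The power to detect differences in longitudinal DLQI effects between the intervention and control group will be 56"%. The one-tailed figure is 68%. For communication, with improvements of 0.8 and 0.4 SD, the figure is 80%.

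The Statistical analysis section lists the terms of the model:

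- at patient level: "Longitudinal models will have a random intercept to account for individual differences at baseline";
- for time and arm, in a single list: "fixed regression coefficients for each of the measurement occasions following baseline, for the intervention effect";
- as further fixed terms, coefficients "for study sites (to account for differences between sites), and for possible other explanatory variables (such as age and sex").

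It adds that the authors will investigate the longitudinal structure, "whether one or more of the fixed regression coefficients should be considered random, and whether there are interaction effects".

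Design of the study says that sites, not patients, are randomized, and places visits at weeks 0, 6, 12, 24, 36 and 48. Outcome measures says that patients complete the set of questionnaires at the end of each consultation.

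**The concern.** A difference in change between arms is an intervention-by-visit contrast. In the listed model the occasion terms start after baseline, so week 0 is a modelled response and serves as the reference. The intervention enters once, and any interaction is only a matter for investigation. The term that would test the powered hypothesis is therefore not fixed in advance.

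Three things are at stake. The coefficient reported as the intervention effect might not be the quantity the sample size addresses. A chance difference at baseline between arms built from only 18 sites could enter it. And the baseline DLQI, which is collected anyway, is not used to gain precision on a primary outcome that the plan itself puts at 56% power.

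**Working it through.** **Inputs from the Power calculation section.** Difference in change 1.0 − 0.7 = 0.3 SD for the DLQI and 0.8 − 0.4 = 0.4 SD for communication; n = 100 per arm; two-sided alpha 5%; correlation 0.5; DLQI SD 7.0 points. Power below is Φ(ncp − 1.96), unless 16 df is stated.

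**1. The plan's own figures.** SD of change = √(2(1 − 0.5)) = 1.0 SD.

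- DLQI: ncp = 0.3/√(2/100) = 2.121, power 56.4% two-sided and 68.3% one-sided (stated: 56% and 68%).
- Communication: ncp = 0.4/√(2/100) = 2.828, power 80.7% (stated: 80%).

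So the stated powers are for an unadjusted difference in change, without allowance for clustering.

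**2. A time-constant coefficient without site terms.** In balanced data with a random intercept, it equals the arm difference in patient means over all modelled visits. Take the induction visits (weeks 0, 6, 12, 24) and assume the correlation of 0.5 holds between every pair. The effect profile is also an assumption, since the article gives none.

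| Assumed profile (SD) at weeks 0, 6, 12, 24 | Coefficient | DLQI points |
|---|---|---|
| 0, 0.3, 0.3, 0.3 | 0.9/4 = 0.225 SD | 0.225 × 7 = 1.6 |
| 0, 0.075, 0.15, 0.3 | 0.525/4 = 0.131 SD | 0.131 × 7 = 0.9 |

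The target is 0.3 × 7 = 2.1 points. A chance baseline difference of 0.2 SD with no true effect passes in full into this coefficient and cancels in a difference in change.

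**3. The same coefficient with the listed fixed site terms.** Columns for four visits and 18 sites: 1 intercept + 3 occasions + 1 intervention + 17 sites = 22. The rank is 21: the intervention column is a combination of the intercept and site columns, so it cannot be estimated. If the intervention is coded as zero at baseline, the rank is 22 of 22 and the term is estimable.

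**4. Baseline adjustment at the plan's correlation.** Residual variance is 1 − 0.5² = 0.75, against 1.0 for the change score. DLQI: ncp = 0.3/√(0.75 × 2/100) = 2.449, power 68.8%.

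**5. With clustering.** The article gives no ICC, so a range is assumed. Mean cluster size is 200/18 = 11.1, the design effect is 1 + 10.1 × ICC, and the test uses 18 − 2 = 16 df.

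| Assumed ICC | Design effect | Change score | Baseline-adjusted |
|---|---|---|---|
| 0.01 | 1.10 | 48% | 59% |
| 0.05 | 1.51 | 37% | 47% |
| 0.10 | 2.01 | 29% | 37% |

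These rows apply the same ICC to the adjusted and the unadjusted contrast.

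**The case against.** The strongest reply is that the coding of the intervention term is not stated. With fixed sites only a post-baseline coding can be fitted, so a charitable reader may take that as the intent. It would estimate an average post-baseline difference in change. With the fixed site terms absorbing each arm's level, the variance of the mean of three post-baseline visits minus baseline is 2/3 + 1 − 2 × 0.5 = 0.667. Power is then 74% for a full effect from week 6 and 33% for linear growth (mean effect 0.525/3 = 0.175 SD), ignoring clustering. This stands: power is not necessarily lost, and the averages in step 2 illustrate one reading only. It does not remove the point, because the article neither states that coding nor names the contrast.

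A second reply is that an article leaves covariance structure, covariates and coding to the full protocol or analysis plan, and that age and sex are only examples, so a baseline covariate is not excluded. That is fair for the detail. But the article lists the model term by term, and the terms listed do not contain the powered contrast. The random intercept models within-patient correlation; it does not adjust a time-constant between-arm coefficient for baseline.

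Stronger readings are tempting and not supported:

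- A reader might infer that the trial will report a diluted effect. That needs the time-constant coding, omission of the listed site terms and an assumed effect profile.
- A reader might infer that exploring model structure inflates the type I error. Nothing in the article allows that to be quantified, and choosing a covariance structure is ordinary practice.
- A reader might infer that no effect can exist at week 0. If the end-of-consultation timing covers the DLQI, the first DLQI follows the first Skindex-29 discussion, and the communication questionnaire necessarily follows that consultation.

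**Conclusion.** The point holds as a mismatch between the powered contrast and the stated model. The sample-size figures rest on a difference in change to end of induction, and the model fixes no term for it. Read as constant over time, the single coefficient is either an average that includes week 0 or, with fixed sites, not estimable; which reading was meant cannot be settled from the article. The gain from adjusting for baseline DLQI is 56% to 69% before clustering, or about 8 to 12 percentage points over the assumed ICC range of 0.01 to 0.10. It rests on the plan's correlation of 0.5 and on a first DLQI taken before the intervention starts.

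**What to change.** Prespecify one primary mixed model for the DLQI:

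- visit as categorical, with intervention-by-visit terms;
- the arm difference at week 24 (end of induction) as the primary contrast, because the power calculation is set there;
- adjustment for baseline DLQI;
- site terms that leave the contrast estimable, for example a random site effect.

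Report the exploration of covariance structure, random slopes and further interactions as secondary or sensitivity analyses.

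Confirm first that the week-0 DLQI is completed before the first Skindex-29 consultation. If it is not, neither baseline adjustment nor an equal-baseline constraint is valid: use the unconstrained intervention-by-visit contrast and state the limitation. Do not adjust communication for its first-visit score, which is measured after the intervention has begun.

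The cost is a change of analysis wording and a check on questionnaire timing; no further data are needed.
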